### Sample size

A total of 80 patients will be randomized, with 40 patients assigned to each treatment arm. A loss of follow up at one year of 2.5% is considered realistic and it has been calculated to account for a dropout rate of 10%.

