### Randomization

Eligible patients, who give confirmed consent, are randomly assigned to one of the two operating techniques. Randomization will be performed using sequentially numbered, sealed, opaque envelopes. Computer-generated block randomization is used to ensure an equal number of patients in each treatment group. The block size used is not available from the study protocol and is unknown to the investigator, to keep the potential for selection bias at the lowest level possible. Patients will be allocated to a study group by the operating surgeon immediately prior to the operation.

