### Statistical analyses

#### Sample size

If LMGB is non-inferior to LRYGB, 72 patients are required (36 patients per study arm) to have an 80% chance that the lower limit of the one-sided 97.5% confidence interval (equivalently a 95% two-sided confidence interval), does not include the non-inferiority limit of –10% EWL when assessed at 12 months. Given an anticipated dropout rate of 10%, the total number of patients to be included in the study is 80 (40 patients per arm). The non-inferiority limit of –10% EWL was chosen based on expert bariatric opinion. Furthermore a standard deviation of 15 was assumed in both arms according to a study from Lee et al. [9]. For further details on calculations see “Analysis of endpoints”.

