#### Analysis of secondary endpoints

To investigate non-inferiority of the experimental treatment in the long term, analysis used for the primary endpoint will be repeated for EWL at 36 months post-surgery. All other endpoints will be analyzed under the assumption of superiority of the experimental treatment compared to the standard treatment. To compare the duration of surgery and the length of hospital stay between the two treatment groups, the Wilcoxon signed-rank test will be conducted (as we assume the data to be right-skewed).

The number of perioperative and postoperative complications will be analyzed by the chi-squared test or Fisher’s exact test, dependent on the observed numbers in a 2 × 2 contingency table. Additionally, we will compare the risk for complications in the two groups by calculating the risk difference with 95% confidence interval. The other secondary endpoints will be investigated using appropriate explorative methods and graphical visualization.

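### Operating time and hospital stay are to be compared between two unpaired arms with a paired test (Wilcoxon signed-rank)

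*Protocol article*

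**What the plan says.** The Analysis of secondary endpoints section gives the purpose and the test in one sentence. The purpose is "To compare the duration of surgery and the length of hospital stay between the two treatment groups". The method is that "the Wilcoxon signed-rank test will be conducted (as we assume the data to be right-skewed".

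The design is set out elsewhere in the same article:

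- Randomization: "Eligible patients, who give confirmed consent, are randomly assigned to one of the two operating techniques", and "Computer-generated block randomization is used to ensure an equal number of patients in each treatment group".
- Sample size (under Methods/Design): "A total of 80 patients will be randomized, with 40 patients assigned to each treatment arm".
- Analysis of endpoints: the per-protocol population is primary for the study endpoints. It leaves out protocol violators, including patients who changed group or have missing measurements. The intention-to-treat population is used for sensitivity analysis.

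**The concern.** The signed-rank test takes one difference per pair, ranks the absolute differences and sums the ranks by sign. It needs either two measurements on the same unit or units matched by design. Operating time and length of stay are each observed once per patient, and the two values being compared belong to different patients in different arms. There is no difference to rank until someone decides which LMGB patient is set against which LRYGB patient, and the article gives no rule for that.

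Two things follow. With equal arms the result depends on the order in which patients are listed, so the analysis is not truly pre-specified. With unequal arms the test is undefined unless patients are dropped. The analyst must then either depart from the published plan or report a p-value that another listing order would change. Apart from 36-month EWL and complications, these are the only secondary endpoints for which the article names an analysis.

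**Working it through.** **1. The plan's own figure, to see whether this point touches it.** Inputs from the Sample size section under Statistical analyses: margin 10, SD 15, one-sided 2.5%, power 80%, true difference taken as 0.

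n per arm = 2 × (1.960 + 0.842)² × 15² / 10² = 2 × 7.85 × 2.25 = 35.3, rounded up to 36. This gives 72 in total, and 72 / 0.90 = 80. The stated 72 and 80 are reproduced. They rest on a comparison of mean EWL and do not involve the test at issue.

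**2. Test against design.**

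| Signed-rank test needs | Trial provides |
|---|---|
| Pairs, or one sample of differences | Two parallel arms, each patient assigned one technique |
| A pairing rule | None stated; block randomization serves only to balance numbers |
| Equal numbers on both sides | 40 and 40 at randomization, not guaranteed after per-protocol exclusions |

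**3. How often the arms would be unequal.** Assume each of 40 patients per arm is excluded independently with probability p. The range 2.5% to 10% is borrowed from the loss and dropout rates in the Sample size section; the article gives no exclusion rate for these two endpoints. Let X and Y be the numbers excluded, each Binomial(40, p). Then P(unequal) = 1 − Σₖ P(X = k)².

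- p = 0.025: 1 − 0.31 = 0.69
- p = 0.10: 1 − 0.15 = 0.85

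**4. Dependence on the pairing in one data set.** Assumed log-normal times, 40 per arm, log means 4.30 and 4.45, log SD 0.30. The data were held fixed and one arm was re-ordered at random 2,000 times.

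- Rank-sum: p = 0.089, the same for every ordering.
- Signed-rank: p from 0.008 to 0.307, median 0.087; 18% of orderings fell below 0.05.
- With 36 against 37 patients the signed-rank calculation fails.

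**5. Repeated data sets.** Assumed log-normal, 36 per arm, log SD 0.35, one arm 18% shorter, two-sided 5%.

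- Power: about 64% for rank-sum and 62% for signed-rank.
- At least one of 100 random pairings changed the verdict in 39% to 47% of data sets, depending on the simulation run. This count grows with the number of pairings tried.
- On a stricter count, with 10% to 90% of pairings significant, about a quarter of data sets were split.
- A single arbitrary signed-rank run disagreed with the rank-sum verdict in about 10% of data sets, and in about 3% when there was no true difference.
- Type I error: between 4% and just over 5% for both tests.

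**The case against.** The strongest reply is that this is a naming slip. The sentence announces a between-group comparison and gives skewness as the reason, which is what one would write before naming the rank-sum test. An analyst with no pairing variable would notice at once. The consequences are also modest. Only two secondary endpoints are involved, the primary confidence interval for mean EWL is unaffected, arbitrary pairing does not inflate the false-positive rate, and about two points of power are lost. The simulated effect sits where power is near 65%, so verdicts flip easily, and the any-flip percentage is close to a worst case. None of the distributions comes from the article. Nor does the article tie these endpoints to a formal claim that LMGB is simpler; the Background mentions lower technical demand only as a suggestion.

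All of that stands as a limit on severity. It does not remove the error. A specific test is named, so this is not detail left to a fuller plan. The article gives no pairing that would rescue the test: block size is deliberately undisclosed, and nothing says the analysis pairs patients within blocks. That the right test can be guessed is a reason to correct the text, not to leave it.

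**Conclusion.** The concern holds. The named test does not fit two independent arms. What is wrong is that the result is arbitrary, and that the test cannot be computed when the arms differ in size; false-positive risk is not inflated. The mismatch follows from the text alone and needs no assumption. The sizes given for it do: log-normal data with assumed spread and effect for the p-value range and verdict changes, and independent exclusions at 2.5% to 10% for the 69% to 85% chance of unequal arms. The 10% disagreement with the rank-sum test is the fairest single measure of practical effect in the scenario used. With only two secondary endpoints affected, this should be corrected before analysis but does not threaten the trial's main conclusion.

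**What to change.** In Analysis of secondary endpoints, replace the signed-rank test with the Wilcoxon rank-sum (Mann-Whitney U) test for duration of surgery and length of hospital stay. Make the same correction in the full protocol or statistical analysis plan if the wording was carried from there. A Hodges-Lehmann estimate of the shift with a 95% confidence interval would be a useful addition but is not part of the correction.

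The cost is a word or two. The data collected, the 72 evaluable and 80 randomized patients, and the primary analysis stay as they are. The Trial status section says enrollment was not yet complete, so at the time of the article the change could still be made and dated before analysis.

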### Ethical considerations

Participation in this trial is strictly voluntary and patients are allowed to exit the trial at any point without explanation. All eligible patients are provided an information sheet describing the study with sufficient information for them to make an informed decision about their participation in this study.

The study protocol, patients’ information sheets and informed consent forms were approved by the local ethics committee (Kantonale Ethikkommission Zürich, KEK-ZH 2013-0389). In addition, insurance coverage for general liability has been obtained. Patients who decline to participate in this study are treated according to clinical standards. These patients will not be included and no study-specific follow up will be performed.

### Participants’ confidentiality

The participants’ confidentiality is maintained at all times. For confidentiality reasons, case report forms (CRF) do not contain any personal data on study participants. Members of the ethics committees are obliged to respect confidentiality and to refrain from divulging the participants’ identities or any other personal information they might be aware of. Source data in the hospital’s electronic patient information systems are secured by personal passwords and handled with respect to medical secrecy.

### Archiving and data retention

The investigator will maintain all study-related records, such as CRFs, medical records, laboratory reports, informed consent documents, safety reports, information regarding participants who discontinued the trial and other pertinent data. All records will be retained by the investigator as long as required by the applicable laws and regulatory requirements (10 years). Thereafter, all data will be destroyed. The study is conducted in compliance with this protocol and according to Good Clinical Practice standards and legal regulations. Serum and plasma samples will be stored in –80 °C freezers located in the laboratories where the measurements will be performed, which are the Center for Molecular Cardiology, Institute of Veterinary Physiology at the University of Zurich and the Laboratory of Translational Nutrition Biology at the Federal Institute of Technology (ETH) Zurich.

Freezers are provided with systems for 24-hour monitoring 7 days a week and reporting of temperature control with immediate remote alarm notification and continuous data collection. This provides reliable and durable environmental conditions for temperature requirements of our samples. The serum and plasma samples will be stored for up to 5 years after the completion or termination of the study. After this period, samples will be disposed of as biohazardous waste following policies in force at the University of Zurich and at ETH Zurich for the handling and disposal of biohazardous material. At the completion of the study, there will be a final reconciliation of samples collected, samples used and samples remaining. This reconciliation will be reported on a samples accountability form, signed and dated. All stored samples will be coded with a unique storage identifier. The list of patient identifiers is accessible to UZ, TD, MK and EO. The scientists who will carry out analyses on these materials are all experienced researchers. They will not have access to personal identifiers and will not be able to link the results of these tests to personal identifier information. Access to the study results will be restricted. A password system will be utilized to control access. These passwords will be changed on a regular basis. All reports prepared within this study will be prepared such that no individual subject can be identified.

## Discussion

The positive effects of bariatric surgery on weight loss and obesity-related comorbidities and mortality have been widely demonstrated in long-term cohort trials and short-term RCTs [6, 7, 18]. Over time, these procedures have improved in respect to safety and can be offered at a low mortality and morbidity rate [9, 19]. Various surgical options are available, with LRYGB and laparoscopic sleeve gastrectomy (LSG) being the two most common procedures. In addition, there are many new operations, one of them being the LMGB. The quest for the most effective bariatric procedure is not yet completed as weight loss and improvement of metabolic status, comorbidity and quality of life have only been evaluated in a few randomized controlled trials over a short-term period. This study investigates the effectiveness of LMGB compared to LRYGB, analyzing defined clinical endpoints such as EWL, morbidity and mortality, metabolic changes and quality of life. In addition, the RCT will also answer some important questions about LMGB, such as the course of obesity-related comorbidities and dumping syndrome.

Furthermore, this study addresses the postoperative course of hormones and lipids in these two different bariatric procedures. It has been shown that after bariatric operations the levels of hormones such as GLP-1 and PYY are markedly increased [20]. Surgery improves obesity-associated pro-atherogenic dyslipidemia as well, which is characterized by high LDL and TG and low HDL-C plasma levels. Low HDL-C levels are associated with increased cardiovascular disease risk [21]. It was recently demonstrated that RYGB improved the endothelial protective properties of HDL in obese patients; 12 weeks after RYGB these properties were comparable to those of healthy subjects although the patients were still obese [22, 23]. Overall, the data indicate that RYGB may achieve a dual HDL benefit, first the rapid restoration of quality to more “healthy” HDL, and second the increase in circulating HDL levels in the longer-term period. The influence of LMGB on changes in lipoprotein profile and function and bile acids are not yet known.

One issue surrounding LMGB that remains highly controversial is the reflux of bile into the gastric pouch and potentially into the esophagus. LMGB is often compared to the refluxogenic loop gastric bypass (LGB) described by Mason et al. [24], which consists of a large gastric pouch transected horizontally with the gastrojejunostomy close to the gastroesophageal junction. However, LMGB consists of a long narrow vertical gastric pouch, thus, reflux into the esophagus is not believed to be an LMGB-specific problem. By contrast, the surgical technique of LMBG is comparable to the Billroth II procedure performed in peptic ulcer disease and gastric cancer. In LMBG and Billroth II, the most important parallel is the single anastomosis bypass of the duodenum without a Roux-limb. The LMGB distance of the gastrojejunostomy to the esophagus is longer than in Billroth II. Furthermore, the biliopancreatic limb in LMGB measures 200 cm compared to 60–80 cm for the Billroth II operation.

In conclusion, the perfect bariatric procedure is technically easy and safe, and leads to adequate EWL and improvement in obesity-related comorbidities. In contrast to the widely used LRYGB and LSG, the LMGB might fulfill all of these criteria. The current study will answer questions about safety, effectiveness and pathophysiological changes in obesity-relevant hormones and lipids after LMGB. These findings might therefore influence decision-making in bariatric surgery implementing current surgical protocols towards personalized indications.

## Trial status

The trial has received ethics approval, and enrollment in the trial has begun but has not yet reached full enrollment.

## Abbreviations

BAROS: Bariatric Analysis and Reporting Outcome System
BMI: Body mass index
CRF: Case report form
EGD: Esophagogastroduodenoscopy
EW: Excess weight
EWL: Excess weight loss
GERDQ: Gastroesophageal Reflux Disease Questionnaire
GIQLI: Gastrointestinal Quality of Life Index
GLP-1: Glucagon-like peptide 1
HDL: High density lipoprotein
IBW: Ideal body weight
ITT: Intention-to-treat
LDL: Low density lipoprotein
LMGB: Laparoscopic mini gastric bypass
LRYGB: Laparoscopic Roux-en-Y gastric bypass
PP: Per protocol
PYY: Peptide YY
QOL: Quality of life
RCT: Randomized controlled trial
RYGB: Roux-en-Y gastric bypass
SMOB: Swiss Study Group for Morbid Obesity
SNAQ: Simplified Nutritional Appetite Questionnaire
SPIRIT: Standard Protocol Items: Recommendations for Interventional Trials
TG: Triglycerides
